## Abstract

**Background:**

Prevention of neurodevelopmental impairment due to preterm birth is a major health challenge. Despite advanced obstetric and neonatal care, to date there are few neuroprotective molecules available. Melatonin has been shown to have anti-oxidant/anti-inflammatory effects and to reduce brain damage, mainly after hypoxic ischemic encephalopathy. The planned study will be the first aiming to evaluate the capacity of melatonin to mitigate brain impairment due to premature birth.

**Method:**

In our planned prospective, multicenter, double-blind, randomized vs placebo study, we will recruit, within 96 h of birth, 60 preterm newborns with a gestational age ≤ 29 weeks + 6 days; these infants will be randomly allocated to oral melatonin, 3 mg/kg/day, or placebo for 15 days. After the administration period, we will measure plasma levels of malondialdehyde, a lipid peroxidation product considered an early biological marker of melatonin treatment efficacy (primary outcome). At term-equivalent age, we will evaluate neurological status (through cerebral ultrasound, cerebral magnetic resonance imaging, vision and hearing evaluations, clinical neurological assessment, and screening for retinopathy of prematurity) as well as the incidence of bronchodysplasia and sepsis. We will also monitor neurodevelopmental outcome during the first 24 months of corrected age (using the modified Fagan Test of Infant Intelligence at 4–6 months and standardized neurological and developmental assessments at 24 months).

**Discussion:**

Preterm birth survivors often present long-term neurodevelopmental sequelae, such as motor, learning, social-behavioral, and communication problems. We aim to assess the role of melatonin as a neuroprotectant during the first weeks of extrauterine life, when preterm infants are unable to produce it spontaneously. This approach is based on the supposition that its anti-oxidant mechanism could be useful in preventing neurodevelopmental impairment. Considering the short- and long-term morbidities related to preterm birth, and the financial and social costs of the care of preterm infants, both at birth and over time, we suggest that melatonin administration could lead to considerable saving of resources. This would be the first study addressing the role of melatonin in very low birth weight preterm newborns, and it could provide a basis for further studies on melatonin as a neuroprotection strategy in this vulnerable population.

**Trial registration:**

ClinicalTrials.gov NCT04235673. Prospectively registered on 22 January 2020.

## Introduction

### Background and rationale {6a}

The birth rate in Italy is approximately 552,000/year and 1% of these newborns are very low birth weight infants (≤ 1500 g at birth) or born at a gestational age (GA) of ≤ 29 weeks + 6 days [1]. Preterm birth survivors often present long-term neurodevelopmental sequelae, such as motor, learning, social-behavioral and communication problems [2–4]. Diffuse white matter (WM) damage, connectivity defects, and dysmaturational disturbances of cerebral WM and gray matter structures are now recognized to constitute the neuropathological substrate of these difficulties [5]. Magnetic resonance image (MRI) findings confirm that the WM is very susceptible to preterm birth-related injury [6], and recent studies [5] have shown that interventions aiming to prevent or mitigate “encephalopathy of prematurity” (i.e., this combination of WM injury and gray matter structural disturbances) may be possible.

Among the most promising molecules in this scenario, melatonin (ME) can be considered a prime candidate for conferring neuroprotection in preterm infants. This hormone and its metabolites are highly efficient anti-oxidants and free radical scavengers. ME is metabolized in the liver, but can also be metabolized by free radicals and oxidants and converted into c3-hydroxyME, which, in turn, directly scavenges free radicals. In the brain, it is metabolized into kynurenine derivatives, which are responsible for its anti-oxidant/anti-inflammatory response [7, 8]. ME has already been shown to act as a neuroprotectant in adult cerebral ischemia [9], and an increasing number of studies have consistently demonstrated that ME protects the developing brain by preventing the abnormal myelination and inflammatory glial reaction [10, 11] that are the main causes of WM injury [12]. ME has also been shown to be capable of reducing brain damage after neonatal hypoxic ischemic encephalopathy (HIE), and of preventing preeclampsia-related impairments, intrauterine fetal growth restriction, ventilation-induced damage and bronchopulmonary dysplasia (BPD) [13–16]. In prospective trials on newborns with HIE [17, 18], intravenous ME was shown to improve brain injury outcomes and significantly reduce concentrations both of the lipid peroxidation product malondialdehyde (MDA), and of nitrite/nitrate. Moreover, numerous ongoing trials dealing with ME administration in neonates (registered on ClinicalTrials.gov) report the absence of adverse events (AEs) linked to ME, and confirm its usefulness in the neonatal setting (i.e., in HIE). The fetus does not secrete ME but receives it by transplacental transfer, according to the maternal circadian secretion pattern. Functional production of ME is not established until about 12 weeks after birth, although a breastfed newborn can take advantage of maternal ME, whose concentration increases at night [19]. Conversely, preterm infants are deprived of the maternal ME they would normally have received during the last weeks/months of pregnancy and, moreover, their endogenous production of the hormone may be delayed even by months [20]. Therefore, exogenous ME administration during the first weeks of extrauterine life could help in preventing/mitigating the negative effects of prematurity on brain development.

Moreover, the pharmacokinetics of ME in preterm infants [19] show prolonged half-life and clearance and a decreased volume of distribution. The results of another pharmacokinetic study [21] highlighted the possibility of maintaining active concentrations of ME in blood through a single oral administration repeated every 12/24 h.

Until now, no study in very preterm infants has attempted to assess the capacity of ME to protect the brain against oxidative stress-induced impairment caused by preterm birth. This is the aim of our project, as we believe that improved knowledge in this area could influence, and even permanently modify, neurodevelopmental outcome in preterm infants. From the relevant literature on preterm [19, 21] and term infants [13–18], we merged all the available information about dosage, administration route, dosing interval and duration of treatment. Considering the novelty of the trial, the dosage of 3 mg/kg/ day for 15 days has been chosen.

### Objectives {7}

This study has 3 specific aims:
To measure, in a sample of preterm newborns, after 15 days of blind administration of ME or placebo, plasma MDA and its correlation with plasma ME (primary aim of the study).To evaluate at term-equivalent age (TEA 40 weeks) whether, after 15 days of ME administration, infants have a better clinical and instrumental outcome, as shown by a reduction of neonatal morbidities such as BPD, infection/sepsis, hearing impairment, visual impairment (retinopathy of prematurity (ROP) or abnormal visual behavior), pathological neurological examination, and brain injury evaluated with cerebral ultrasound (cUS) and brain MRI.To assess the infants’ neurodevelopmental outcome, correlating the results with the ME vs placebo treatment. More specifically, at 4–6 months of corrected age (CA), we will assess novelty preference and fixation duration using the eye-tracking-modified Fagan Test [22], which is moderately predictive of later cognitive abilities; at 18–24 months of CA, outcome will be assessed using anthropometric measurements, neurological and developmental evaluations and standardized developmental surveys administered to parents.

### Trial design {8}

The planned study will have a superiority, prospective, multicenter, parallel-groups, randomized, double-blind vs placebo-controlled design. Participants will be randomly allocated to the intervention group or the control group, in a 1:1 ratio. The intervention period will last 15 days. Preterm comorbidities and neurodevelopmental outcome will be evaluated throughout the first 24 months of CA. Table 1 shows the assessments to be administered at baseline and immediately post-intervention. This trial protocol is designed in accordance with the Standard Protocol Items: Recommendations for Interventional Trials (SPIRIT) 2013.

**Table 1 Tab1:**
[figure not shown]
Standard Protocol Items: Recommendations for Interventional Trials (SPIRIT) figure with timeline for recruitment, assessments, and interventions

*Abbreviations*: *BAERs* brainstem auditory evoked responses, *BDP* bronchopulmonary dysplasia, *CA* corrected age, *CBCL* Child Behavior Checklist, *cUS* cerebral ultrasound, *D* day, *GA* gestational age, *GMs* general movements, *M* month, *MDA* malondialdehyde, *ME* melatonin, *MRI* magnetic resonance image, *NAVEG* Neonatal Assessment Visual European Grid, *NNNS* Neonatal Intensive Care Unit Network Neurobehavioral Scale, *ROP* retinopathy of prematurity, *W* week

## Methods: participants, interventions, and outcomes

### Study setting {9}

The role of coordinating center will be shared by the Fondazione IRCCS Policlinico San Matteo, Pavia, and the IRCCS Mondino Foundation, Pavia, while the collaborating center will be the ASST “Spedali Civili” Children’s Hospital in Brescia (where the local ethics committee approval process is still ongoing). Preterm newborns will be recruited within 96 h of birth at the two centers’ neonatal intensive care units (NICUs). ME and placebo will be administered at these NICUs. Plasma concentrations of MDA and ME will be determined at the laboratory of the coordinating center. Staff at the collaborating center’s NICU will therefore send cryopreserved neonatal plasma samples to the coordinating center. The assessments scheduled to take place at TEA will be performed at the NICU of birth. Follow-up assessments, scheduled to take place at 4–6 months and at 18–24 months of CA, will be performed at the Child Neuropsychiatry Units of Pavia and Brescia.

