### Sample size {14}

The literature contains only one paper sufficiently similar to our study [30]; this paper was taken as a reference source to select the primary outcome (MDA concentration in the two groups) and calculate the sample size for our proposed study. A total of 26 patients per group is deemed sufficient to detect, with a power greater than 80%, a statistically significant difference equal to 8 nmol/ml (standard deviation in the two groups equal to 7) between the null hypothesis (H_0_) of the same concentration of MDA 16 nmol/ml in the two groups and the alternative hypothesis (H_1_) of an MDA concentration reduction to 8 nmol/ml in group 2 (*t*-test for independent groups with alpha error = 5%). Considering a potential dropout rate of 15%, 30 newborns per group will be enrolled.

All the participating patients will be enrolled by the two participating NICUs.

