### Recruitment {15}

The recruitment will be done at Fondazione IRCCS Policlinico S. Matteo, Pavia, Italy (joint coordinating center) and ASST "Spedali Civili” di Brescia, Brescia, Italy (participating center). The coordinating center obtained the necessary legal permission to start the trial earlier than the participating center, which is currently awaiting ethical approval. Both hospitals are third-level centers and accept newborns from 23 weeks of GA onwards. The principal investigator (PI) and the other neonatologists participating in the trial actively work on the wards, with schedule timing that guarantees the constant presence (24 h per day) of the PI or at least one of the co-investigators responsible for recruiting patients, giving adequate information to parents, and following the ongoing study. The centers have an incidence of about 4 to 8 eligible patients/month (patients with GA ≤ 29 weeks + 6 days, able to receive 20 ml/kg/day enteral feeding within 96 h of birth). This should guarantee recruitment of a total of 60 patients (even accounting for dropouts).

The two centers are similar in terms of available instruments, and both have a dedicated child neurology and psychiatry service. The researchers involved in the study have similar high levels of expertise, underwent the same specialist training, and use same methodological tools. Furthermore, most of them have often worked together on other research projects over the past years.

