## Assignment of interventions: allocation

### Sequence generation {16a}

The randomization will be generated by the Unit of Clinical Epidemiology and Biometry (unblinded team) at the coordinating center, according to a 1:1 allocation ratio, by means of computer-generated random numbers that will allow for extra patient allocations in the event of dropouts. The randomization sequence will be generated by a random number generator at the same unit. The PIs of the two NICUs will sequentially allocate the participants to the two groups on the basis of the generated lists.

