## Statistical methods

### Statistical methods for primary and secondary outcomes {20a}

With regard to analysis of the trial results, a normality test (Shapiro-Wilk test) will be used to determine whether datasets are well modeled by a normal distribution. Categorical variables will be described as counts and percentages and compared between treatment groups by chi-squared test or Fisher’s exact test. Continuous variables will be expressed as mean and standard deviation or median and interquartile range, and comparisons between treatment groups will be made using the *t*-test for independent groups or an analogous non-parametric test if the variable is not normally distributed. Potential multivariate analysis will be performed with regression models. To account for non-independence of observations in case twins are enrolled, general estimating equations (GEE) or mixed regression models will be used. Statistical analysis will be performed by the Clinical Epidemiology and Biometry Unit at the coordinating center using the STATA statistical package (Stata, release 16 or later, StataCorp, College Station, TX, USA).

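### The primary MDA comparison has no centre term and allocation is not stated to be stratified by centre, so any between-centre shift in measured MDA adds avoidable noise, though not bias

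*Protocol article*

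**What the plan says.** - **Samples.** Study setting {9} places the MDA and melatonin assays at the coordinating centre and says that Brescia staff "will therefore send cryopreserved neonatal plasma samples to the coordinating center". The aim 1 text under Plans for assessment and collection of outcomes {18a} gives one blood-sampling procedure, one laboratory and two time points (recruitment and after 15 days). Neither section says whether Pavia plasma is assayed fresh or is also frozen and batched.
- **Calendar.** Recruitment {15}: "The coordinating center obtained the necessary legal permission to start the trial earlier than the participating center".
- **Allocation.** Sequence generation {16a} describes a computer-generated 1:1 sequence and adds: "The PIs of the two NICUs will sequentially allocate the participants to the two groups on the basis of the generated lists". Centre is not named as a stratum.
- **Analysis.** Statistical methods {20a} says that "comparisons between treatment groups will be made using the" independent-groups t-test, or a non-parametric counterpart if the variable is not normal. Regression is mentioned only as a possibility, with no covariates named. GEE or mixed models are reserved for twins.
- **Planning values.** Sample size {14} plans 26 per group for "a statistically significant difference equal to 8 nmol/ml", with "standard deviation in the two groups equal to 7", and 30 per group after dropout.

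**The concern.** MDA is the primary outcome. One centre's samples are frozen and transported before assay, and that centre starts later, so its measured values could sit at a different level for reasons unrelated to treatment. The article promises harmonisation between centres for the MRI scans, a secondary outcome, but has no matching sentence for the primary marker.

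If such a shift exists, the stated analysis has nothing to absorb it:

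- If allocation is not stratified by centre, the arms can by chance hold different shares of Brescia infants, and the shift then moves the estimate in that particular trial.
- If allocation is balanced within centre, the estimate is protected, but an unadjusted test still counts the shift as residual variation and is less sensitive than it should be.

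What is at stake is precision.

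**Working it through.** **Inputs from the article.** Difference 8 nmol/ml (16 against 8), SD 7, alpha 5% (taken as two-sided, since sidedness is not stated), 26 evaluable and 30 enrolled per arm, 1:1 allocation.

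**Assumed, because not given.** Between-centre shift d of 2, 4 or 7 nmol/ml, with 14 as an extreme; centre share p of 0.6 (a 60:40 split) or 0.5.

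**1. The plan's own figure.** The normal approximation for 80% power gives 2 × (1.96 + 0.84)² × 7² / 8² ≈ 12.0, rounded up to 13 per group. The exact t-test needs 14, because 13 gives 79.8%. With 26 per group the t-test has 98.1% power. The stated 26 therefore meets the claim of more than 80% power but is well above the minimum for these inputs. (26 equals 2 × 13, so it may be a total read as a per-group number. That is a separate matter; here it means only that there is spare power.)

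**2. Variance inflation from a shift common to both arms.** Ratio = 1 + p(1 − p)d²/49. With p = 0.6:

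| d (nmol/ml) | Calculation | Inflation |
|---|---|---|
| 2 | 0.24 × 4/49 | 2% |
| 4 | 0.24 × 16/49 | 8% |
| 7 | 0.24 × 49/49 | 24% |

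**3. Chance imbalance without stratification.** The difference between arms in centre share has SD √(2p(1 − p)/n). The 95% range of the resulting movement in the estimate is ±1.96 × d × that SD.

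- p = 0.6, n = 30: ±0.50, ±0.99 and ±1.74 nmol/ml for d = 2, 4 and 7.
- p = 0.5, n = 26, d = 7: SD 0.139 × 7 = 0.97, so ±1.90 nmol/ml.

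This movement averages to zero over randomisations and is already reflected in the t-test's standard error.

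**4. Power for a difference of 8, with 26 per arm and p = 0.5.** Total SD = √(49 + 0.25d²). The unadjusted column is from the non-central t distribution; the last column is from 10,000 simulated trials per case.

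| d (nmol/ml) | Total SD | Power, unadjusted | Power, centre term (simulated) |
|---|---|---|---|
| 0 | 7.00 | 98.1% | 98.1% |
| 4 | 7.28 | 97.3% | 98.2% |
| 7 | 7.83 | 95.1% | 98.1% |
| 14 | 9.90 | 81.5% | 97.8% |

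Unadjusted power falls below 80% only when the shift exceeds about 14.6 nmol/ml, close to the assumed control mean of 16.

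**5. Bias and type I error.** In the same simulations, with unstratified allocation and no centre term, the rejection rate under no effect stayed between 4.8% and 5.3%. The mean estimate stayed at about 0 under no effect and about −8 under the planned effect.

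**6. A smaller true effect (assumed).** If the true difference were 5 nmol/ml, power with 26 per arm would be 71% with no shift and 62% with a shift of 7 and p = 0.5. The spare power in step 4 depends on MDA halving.

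**The case against.** The strongest reply has three parts.

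1. *No difference in handling is documented.* The article says where the assay is done and that Brescia sends frozen plasma; it does not say that Pavia plasma is handled otherwise. Freezing times, temperatures and run composition are laboratory-manual detail that an article leaves to the full protocol. This stands. A reader might infer that Pavia samples are assayed fresh, but the text does not say so, and only the shipping step is known to differ. For that reason the handling request is optional.

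2. *Randomisation already deals with it.* A reader might infer that a handling shift biases the treatment comparison. The documents do not support that: allocation is random, 1:1 and double-blind, and nothing suggests that handling depends on arm. The later Brescia start and run-to-run drift are likewise unrelated to arm. This also stands: the shift is noise and chance imbalance only.

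3. *The loss is small, and a covariate can be named in the analysis plan; the plural lists may already be one per NICU.* The loss is indeed small at the planned effect. But the article does commit to an unadjusted comparison as the method, with regression only a possibility, and the plural is compatible with per-centre lists without stating them. A better method at almost no cost remains worth naming.

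**Conclusion.** The point holds as a low-cost gain in precision. The article states an unadjusted primary comparison for a two-centre biomarker trial in which one centre's samples are frozen and shipped, and it does not state stratification by centre. If there is a centre shift, the consequence is extra variance (about 2% to 24% for assumed shifts of 2 to 7 nmol/ml at 60:40) and, without stratification, chance movement of the estimate with a 95% range of up to about ±1.7 nmol/ml at 30 per arm. Power at the planned effect falls by about three percentage points at a shift of one SD, and by more in absolute terms if the true effect is smaller. There is no systematic bias and no inflation of type I error. The sizes rest on assumed shifts and centre shares, and there may be no shift at all. The trial's validity is not in question.

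**What to change.** 1. **Statistical methods {20a}:** make the primary MDA comparison a regression of day-15 MDA on treatment with centre as a fixed covariate. The GEE or mixed model already foreseen for twins can carry the same term.
2. **Sequence generation {16a}:** state that the Biometry Unit generates a separate 1:1 list for each centre, balanced within centre (for example by permuted blocks), since separate lists without such balance would not limit chance imbalance. Make this change together with the first: stratified allocation with an unadjusted test leaves the shift in the error term.
3. **Optional, Study setting {9} and the aim 1 text in {18a}:** confirm that plasma from both centres is frozen by the same procedure and assayed in batches that mix the centres, with each infant's baseline and day-15 samples in the same run.

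Cost: one degree of freedom and a few sentences. No extra infants or blood are needed. If batching is adopted, Pavia results become available later.

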### Eligibility criteria {10}

Thirty preterm newborn infants will be enrolled in each of the two study arms. The enrolled infants will randomly receive ME (3 mg/kg/day) or placebo for 15 days.

The inclusion criteria are:
GA ≤ 29 + 6 (weeks + days)Ability to receive 20 ml/kg/day maternal or formula milk, within 96 h of birthWritten informed consent signed by both the parents.

The exclusion criteria are:
GA > 29 + 6 (weeks + days)Inability to receive minimal enteral nutritionGenetic, congenital, metabolic, and/or TORCH diseasesPeriventricular/intraventricular hemorrhage (PVH/IVH) > grade III [23] and/or periventricular leukomalacia (PVL) ≥ grade II [24] within 96 h of birth (as assessed by cUS)Informed consent denied.

### Who will take informed consent? {26a}

NICU clinicians participating in the investigation will recruit participants and collect informed consent from both the parents. Parents will be fully informed about the study during a counseling session, and then given an information sheet.

